### Objectives {7}

The overall objective of this mechanistic randomized clinical trial is to use transspinal stimulation over the thoracolumbar enlargement, the spinal location of leg motor circuits, to prime locomotor training and ultimately improve the ability to stand and walk in individuals with chronic incomplete SCI. We hypothesize that non-invasive thoracolumbar transspinal stimulation administered before locomotor training increases neuronal responsiveness over multiple spinal segments, mechanistically reflected by increased responses to motor cortex stimulation, and improved phase-dependent modulation of spinal reflexes during walking. Because transspinal stimulation facilitates anti-gravity neuronal circuits, we further hypothesize that transspinal stimulation delivered while participants stand will augment gains compared to delivery in the supine position. To meet our overall objective, 45 individuals with incomplete SCI will undergo 40 sessions of BWS step training primed with 30 Hz transspinal stimulation. Participants are randomized to receive transspinal stimulation during standing (active or sham) or while supine (active).

Our *specific objective 1* determines whether priming locomotor training with transspinal stimulation strengthens corticomotoneuronal connectivity through posture-dependent corticospinal neuroplasticity, as reflected by increased MEP amplitudes and phase-dependent MEP amplitude modulation during stepping. We hypothesize that active but not sham transspinal stimulation delivered during standing increases MEP amplitudes and improves phase-dependent MEP amplitude modulation during stepping. We further hypothesize that transspinal stimulation delivered while supine increases MEP amplitudes but does not induce phase-dependent MEP amplitude modulation during stepping.

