Our *specific objective 2* determines if priming locomotor training with transspinal stimulation evokes appropriate neuromodulation of spinal locomotor networks, as reflected by restored spinal inhibition, reduced neurophysiological hyperreflexia, and re-established phase-dependent soleus H-reflex modulation during stepping. We hypothesize that active but not sham transspinal stimulation delivered during standing (1) restores soleus H-reflex rate-dependent depression, (2) increases the depth of reciprocal inhibition between ankle extensor and flexor muscles, and (3) improves soleus H-reflex phase-dependent modulation towards a more physiological pattern during stepping. We further hypothesize that rate-dependent soleus H-reflex depression and soleus H-reflex modulation during assisted stepping recovers more in the transspinal-standing group than in the transspinal-supine group.

Our *specific objective 3* determines if priming locomotor training with transspinal stimulation improves the ability to stand and walk. Comparing locomotor electromyography (EMG) activity patterns before and after therapy will measure reorganized motoneuron activity and return of reciprocal activation between antagonistic muscles supporting intralimb and interlimb coordination. We hypothesize that the number of motor modules increases in the transspinal-standing group, and that antagonistic muscles show more reciprocal inhibition during stepping.

Our *specific objective 4* establishes clinically functional gains in motor and autonomic function. Improvements in walking ability are assessed with the 10-m test, 2-min test; improvements in balance ability are assessed with the BESTtest. Improvements in bowel, bladder, and sexual function are assessed with questionnaires. Clinical outcomes will be correlated with neurophysiological outcomes to identify predictors of recovery that can be based both on electrophysiological biomarkers and clinical assessment outcomes.

Upon conclusion, this clinical trial will indicate that priming locomotor training with transspinal stimulation improves the ability to stand and walk by facilitation and better synchronization of spinal locomotor neuronal networks and reflex circuits subserving standing and walking. This finding will support that transspinal stimulation works in parallel and not antagonistic to exercise, and can constitute a new standard of care for people with chronic SCI.

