### Outcomes {12}

#### Primary outcomes

The primary outcomes are neurophysiological biomarkers that accurately probe corticospinal and spinal neuroplasticity (at presynaptic and postsynaptic motoneuron levels):Corticospinal neuronal excitability:

We establish the active MEP threshold that corresponds to the intensity that evokes 10 responses of at least 50 mV following 20 1-ms transcranial magnetic stimulation (TMS) pulses in seated subjects. Then, the soleus MEP recruitment input–output curve is assembled while maintaining small-amplitude contractions. During BWS-assisted stepping, MEPs are recorded at 1.3 times the right soleus MEP active threshold randomly at different phases of the step cycle (divided into 16 equal bins or time windows) based on the signal from the right foot switch. During stepping, MEPs are collected before and after intervention using Lokomat settings matched to the baseline, while an effort is made to record MEPs using Lokomat settings matched to those of the last training session. This establishes changes at matched settings and adaptations during more demanding stepping conditions. MEPs recorded at different stimulation intensities (recruitment curve) are measured as peak-to-peak amplitude and normalized to the soleus maximal M-wave (Mmax) evoked by posterior tibial nerve stimulation to counteract differences in muscle fiber composition across subjects. Stimulation intensities are normalized to the intensity corresponding to the 50% of the MEPmax amplitude, estimated based on the sigmoid function fit to the data. For the participants who have obtainable soleus MEPs at baseline, the main outcomes from this experiment are the MEPmax from the MEP recruitment curves and the MEP amplitude at the mid-stance and mid-swing phases before and after the intervention.2)Spinal neuronal excitability:*2a) Soleus H-reflex rate-dependent (or homosynaptic) depression*: To assess restoration of homosynaptic depression exerted at the synapses between muscle spindle primary Ia afferents and alpha motoneurons, soleus H-reflexes following posterior tibial nerve stimulation at the popliteal fossa with a 1-ms pulse are recorded from seated subjects at different frequencies (1.0, 0.33, 0.2, 0.125, and 0.1 Hz). Homosynaptic depression is greatest at 1.0 Hz and fully recovers at 0.125 and 0.1 Hz [69]. Homosynaptic depression cannot be recorded during stepping because it is abolished by strong spinal inhibitory circuits and efferent activity. The main outcome measure from this neurophysiological biomarker is the soleus H-reflex 1.0/0.1 Hz ratio [70].*2b) Soleus H-reflex depression by antagonistic nerve stimulation*: To examine the restoration of reciprocal inhibitory actions on antagonistic alpha motoneurons, the soleus H-reflex is conditioned by common peroneal nerve (CPN) stimulation at conditioning-test (C-T) intervals of 0, 1, 2, 3 and 4 ms, with subjects seated [71–75]. Reproducible CPN conditioning stimulation is ensured by using a stable, small-amplitude TA M-wave and similar soleus M-wave amplitudes under control and conditioning stimulations. Soleus H-reflexes are measured as peak-to-peak amplitude, accepted for M-waves ranging from 2 to 8% of the maximal M-wave (Mmax), and normalized to the Mmax. The main outcome is the amplitude of the conditioned soleus H-reflex as a percentage of the control H-reflex. The C-T interval for which reciprocal inhibition is present or reciprocal facilitation is the smallest is further investigated during BWS-assisted stepping. The main outcomes are the conditioned H-reflex at rest and during the stance and swing phases of BWS-assisted stepping, which both reflect the amount of reciprocal inhibition.*2c) Control and conditioned soleus H-reflexes during stepping*: During standing with BWS as needed, the soleus H-reflex and M-wave recruitment curves are assembled. Then, each participant steps with the assistance of the Lokomat, and soleus H-reflexes are recorded under control conditions and following CPN conditioning stimulation randomly across 16 equal time bins into which each step cycle is divided based on the signal from the foot switch [75]. The tibial nerve stimulation intensity is adjusted in real-time online to evoke H-reflexes such that their corresponding M-waves are 2–8% of the Mmax evoked 80 ms after the test H-reflex at each bin (Fig. 3). Control and conditioned soleus H-reflexes during stepping are collected before (baseline) and 1–2 days after completion of all 40 intervention sessions at Lokomat settings matched to baseline and the last training session. This approach determines changes at matched settings and reflex adaptation at more demanding settings [76]. During stepping, soleus H-reflexes are measured as peak-to-peak amplitude, accepted for M-waves ranging from 2 to 8% of the Mmax, normalized to the Mmax, and averaged for each bin of the step cycle. The main outcome is the control and conditioned soleus H-reflex amplitude normalized to the Mmax at mid-stance and mid-swing phases.

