The soleus H-reflex amplitude during assisted stepping in 11 persons with motor incomplete SCI (AIS C-D) recorded from the right leg was compared before and after locomotor training [26]. Based on the amplitude of the soleus H-reflex at mid-stance before and after training (difference in means of pre versus post: 13.67, pooled standard deviation: 17.4), the effect size was 0.79. To predict sample size at a power of 0.80 at α = 0.05 using a one-way ANOVA across 3 groups, 21 total subjects are needed. We will enroll 45 subjects, so we will be adequately powered even if subjects drop out at a higher than expected 20% rate.

Limb coordination relies on the strength of reciprocal inhibition between antagonistic muscles. We used data from a study performed by our group that examined short-latency inhibition from ankle flexor afferents onto ankle extensor motoneurons at rest in 13 persons with AIS C-D SCI before and after locomotor training [28]. Based on the amplitude of the conditioned H-reflex at the conditioning-test interval of 2 ms before and after training (difference in mean of pre versus post: 15.04, pooled standard deviation: 17.21), the effect size was 0.874. To predict sample size at a power of 0.80 at α = 0.05 using a one-way ANOVA across 3 groups, 18 total subjects are needed. We will enroll 45 subjects, so we will be adequately powered even if subjects drop out at a higher than expected 20% rate. Please note that the established power was based on data from SCI subjects who received either transspinal stimulation or locomotor training separately and not combined.

*Aim 3*: Determine if priming locomotor training with high-frequency transspinal stimulation improves limb coordination and the ability to stand and walk. These are secondary measures, and the study is not powered based on these outcomes.

Collectively, an average of 6 to 8 subjects per group is needed to establish significant differences for primary outcomes before and after transspinal stimulation or locomotor training. By enrolling 15 participants per group, the study will be robustly over-powered to detect these differences despite a projected possible 20% dropout rate, sporadic missing data values, or lower-than-expected observed effect sizes.

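### The hypotheses are about stance–swing modulation, but the stated analysis tests each phase's amplitude separately and fixes no direction of benefit for the mid-swing MEP or the mid-stance H-reflex

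*Protocol article*

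**What the plan says.** Objectives {7}, specific objective 1, states for the standing arms that "active but not sham transspinal stimulation delivered during standing increases MEP amplitudes and improves phase-dependent MEP amplitude modulation during stepping". For the supine arm it predicts larger MEPs but no modulation during stepping, so amplitude and modulation are treated as separate things. Specific objective 2 is to be reflected by "restored spinal inhibition, reduced neurophysiological hyperreflexia, and re-established phase-dependent soleus H-reflex modulation during stepping". Its three numbered hypotheses cover rate-dependent depression, reciprocal inhibition and H-reflex modulation during stepping. Hyperreflexia is not among them, although Aim 2 under Sample size {14} repeats the term.

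Under Primary outcomes, the MEP measures are "the MEPmax from the MEP recruitment curves and the MEP amplitude at the mid-stance and mid-swing phases before and after the intervention". For the H-reflex during stepping, "The main outcome is the control and conditioned soleus H-reflex amplitude normalized to the Mmax at mid-stance and mid-swing phases". No index of modulation is defined.

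Statistical methods {20a} plans a two-way mixed ANOVA with time (2 levels) and group (3 levels), run for each outcome on its own, with Bonferroni post hoc t-tests. Step phase is not a factor. The section on additional analyses {20b} says there will be none.

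**The concern.** The claim and the test are about different quantities. The posture hypothesis in Objective 1 depends on telling larger MEPs from better-modulated MEPs, and an amplitude at one phase cannot do that. Without a stance–swing contrast, a modulation claim would have to be put together afterwards from two separate results, with no rule for combining them.

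The missing direction adds to this. Trial design {8} frames the outcomes as superiority, but for two of the stepping amplitudes the article does not say which way is better. What is at stake is interpretation: a change at a single phase could be presented as support under whichever phrase suits its sign.

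**Working it through.** **1. The plan's own figure.** Sample size {14} uses the mid-stance H-reflex: "Based on the amplitude of the soleus H-reflex at mid-stance before and after training (difference in means of pre versus post: 13.67", pooled SD 17.4. The effect size is 13.67 / 17.4 = 0.786, stated as 0.79. For a one-way ANOVA with three groups and alpha 0.05, noncentrality = N × f². Entering 0.79 as f gives power 0.854 at N = 21, so the stated 21 reproduces. (Whether a pre–post effect belongs there as f is a separate question.) The figure is a single-phase difference with no sign. The other three planning effects are TA MEPmax at rest, the H-reflex at 1.0 Hz, and the conditioned H-reflex at rest. None is a stance–swing difference.

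**2. What the stated tests compare.** Let S and W be a participant's pre-to-post change at mid-stance and at mid-swing. The change in modulation is M = S − W. The group-by-time test on the mid-stance outcome asks whether mean S differs between arms; the one on mid-swing asks the same of W. Neither asks about M. Take effects relative to sham:

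- Both phases rise by a: effects are S = a, W = a, M = a − a = 0. Amplitude grows without modulation, which is what the protocol predicts for the supine MEP.
- Stance rises by a and swing falls by a: effects are S = a, W = −a, M = 2a.

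The single-phase effects have the same size in both cases. Only the sign pattern across two separately analysed outcomes tells them apart, and no rule is given for reading it.

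**3. Direction, side by side.**

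- *Mid-swing MEP.* A rise fits the amplitude part of "increases MEP amplitudes and improves phase-dependent MEP amplitude modulation during stepping". A fall that widens the gap to stance could be offered under the modulation part. No section gives a per-phase direction for the stepping MEP.
- *Mid-stance H-reflex.* A fall could be offered as reduced hyperreflexia. A rise that widens the gap to swing could be offered as re-established modulation. The only per-phase direction in the article is H-reflex depression in swing (Background {6a}). The Transspinal stimulation section associates larger MEPs and smaller H-reflexes with upright balance, not with stepping.

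**4. Error rate.** With no true effect, a two-sided 5% test is significant 5% of the time, 2.5% in each direction. For two outcomes, assumed independent, the chance of at least one significant result is 1 − 0.95² = 0.0975 if either direction counts and 1 − 0.975² = 0.0494 if one does. With Bonferroni over three pairwise comparisons (the number is assumed), one standing-versus-sham contrast has 0.05 / 3 = 0.0167 against 0.0083. A null simulation with 15 per arm (200,000 runs) gave 0.0167 and 0.0084. These pairs only restate two-sided against one-sided testing.

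**5. Precision of the contrast.** If S and W have equal SD σ and correlation ρ, then SD(M) = σ√(2(1 − ρ)). The article gives no ρ. Over an assumed range, SD(M) is 1.41σ at ρ = 0, σ at ρ = 0.5 and 0.63σ at ρ = 0.8.

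**The case against.** The strongest reply is that this is a condensed article with no SAP shown, and a modulation index or a direction of benefit is often set there. That would answer a bare omission. Here, though, the article does fix the main outcomes, the two ANOVA factors and separate analysis of each outcome, and what it fixes does not test the stated hypothesis.

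A second reply is that both phases are named together, so modulation is implicitly a comparison. The intent may well be that, but the stated analysis does not make the comparison.

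Other parts of the defence stand:

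- A reader might infer that these outcomes have no losing direction and that any significant change can be claimed. The documents do not support that. The effect must appear with active and not with sham stimulation, H-reflex modulation must recover more in standing than in supine, and supine stimulation must not induce MEP modulation. Objective 1 joins its two parts with *and*, so a general fall in MEPs contradicts it.
- No section ties hyperreflexia to the mid-stance H-reflex. That reading is open, not stated, and rate-dependent depression is another candidate measure.
- The article does not say that a higher mid-stance H-reflex or a lower mid-swing MEP is the physiological direction.
- The missing sign on 13.67 proves little, since a power calculation needs only a magnitude and none of the planning differences has its benefit direction stated.

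**Conclusion.** The point holds as a mismatch between hypothesis and analysis. Objectives 1 and 2 claim phase-dependent modulation, while the stated analysis tests only single-phase amplitudes. For the mid-swing MEP and the mid-stance H-reflex the direction of benefit is not fixed, so opposite changes can be matched to different phrases of the hypotheses. The hypotheses remain capable of failing.

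A reader might take 9.8% against 4.9% as an inflated false-positive rate. It is not: alpha is unchanged, and those figures assume independence and leave out the planned Bonferroni step. The harm is to what a significant result may be said to show, and no numerical size can be put on that from the documents. It should be corrected before unblinding.

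**What to change.** Before unblinding, which Procedure for unblinding {17b} places at the stage of between-group testing:

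1. Define modulation as the within-participant mid-stance minus mid-swing amplitude, normalised to Mmax, for the stepping MEP and for the control soleus H-reflex. The article states Mmax normalisation for the stepping H-reflex and the MEP recruitment curve, so say the same for the stepping MEP. Name the Lokomat setting used, since more than one is planned after treatment.
2. State the expected direction of each contrast for each arm.
3. Test each contrast group-by-time in the planned mixed ANOVA and rest modulation claims only on it. Report single-phase amplitudes as supporting description.
4. Tie reduced hyperreflexia to one named measure already recorded, with its beneficial direction, or remove the term from Objective 2 and Aim 2. Hmax/Mmax from the standing curves is possible but optional: "During standing with BWS as needed, the soleus H-reflex and M-wave recruitment curves are assembled", and no matching of that support before and after treatment is stated.

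The cost is one derived variable per reflex, with no added visits or participants. Some result patterns can no longer be called success, and if changes at the two phases correlate below 0.5 (with equal SDs), the contrast is noisier than a single-phase amplitude.

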### Participant timeline {13}

The schedule of events for each participant enrolled in this study is presented in Fig. 4. *Enrollment − t*_*1*_*:* Obtain informed consent. Review medical history and medications to determine eligibility based on inclusion/exclusion criteria. Perform medical and neurological examinations needed to determine eligibility based on inclusion/exclusion criteria. Schedule study visits for participants who are eligible and available for the duration of the study. Provide participants with specific instructions needed to prepare for their first study visit, including but not limited to clothing prior to the study. *Baseline visit t*_*1*_*:* Record vital signs. Perform a Lokomat familiarization session. Perform clinical evaluation tests. *Baseline visit t*_*2*_*:* Record vital signs. Record MEPs at rest and during stepping with Lokomat settings obtained from the familiarization session. Provide to the participant the TMS side-effect questionnaire. Record adverse events as reported by participants or observed by investigators. *Baseline visit t*_*3*_*:* Record vital signs. Perform electrophysiological recordings (soleus H-reflex rate-dependent depression and reciprocal inhibition, control, and conditioned soleus H-reflex during BWS-assisted stepping). Record adverse events as reported by participants or observed by investigators. *Intervention visits 4–43:* Administer the assigned transspinal stimulation-locomotor training intervention. Reassess transspinal stimulation threshold and locomotor EMG activity at study Intervention visits *t*_*15*_ and *t*_*30*_. *Final study visits t*_*44*_* and t*_*45*_: Perform clinical evaluation tests and electrophysiological recordings as described in Baseline visits.

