## Statistical methods

### Statistical methods for primary and secondary outcomes {20a}

For each dependent variable (primary and/or secondary outcome), descriptive statistics including frequencies and percentages for categorical variables and means and percentile distributions for continuous variables to examine the distribution of outcomes and describe the study population are performed.

We will group each dependent variable based on the time of testing (before and after the intervention) and the subject group (2 experimental, 1 sham). A two-way mixed analysis of variance (ANOVA) along with Bonferroni post hoc* t-*tests [93] at 2 3 levels (2: time, 3: groups) to test the main and interaction effects among subject groups and time will be performed separately for each outcome. Furthermore, repeated measures analysis of covariance (ANCOVA) will be performed for each outcome separately with gender, age, level of SCI, and clinically evaluated baseline walking function as separate covariates. Outcomes will not be analyzed based on SCI severity because the ISNCSCI scale does not correlate with improvements in walking ability [3], while age is considered one of the predictors of ambulation in SCI [94].

Mixed regression methods and analysis of slope and threshold of correlation will be used to establish the relationship between the ability to stand and walk, quality of life, and changes in primary outcomes (neurophysiological biomarkers). We will use an identity or log link based on the data distribution.

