### Methods for additional analyses (e.g., subgroup analyses) {20b}

There will be no additional analyses.

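### Objective 4 seeks electrophysiological predictors of recovery, but the only biomarker-clinical analysis named uses pre-to-post biomarker change, which can show concurrent association and not prediction

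*Protocol article*

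**What the plan says.** Objectives {7}, specific objective 4, sets the aim: "Clinical outcomes will be correlated with neurophysiological outcomes to identify predictors of recovery". The sentence goes on to describe these as predictors "that can be based both on electrophysiological biomarkers and clinical assessment outcomes", so electrophysiological predictors are explicitly part of the promise.

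Statistical methods {20a} names one analysis that joins the two domains: "Mixed regression methods and analysis of slope and threshold of correlation will be used to establish the relationship". The relationship in question is "the relationship between the ability to stand and walk, quality of life, and changes in primary outcomes (neurophysiological biomarkers" being the biomarker term. The same section plans a repeated measures ANCOVA for each outcome, with gender, age, level of injury and baseline walking function as separate covariates. No baseline biomarker is among them.

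Participant timeline {13} puts the baseline clinical tests at t1, MEPs at t2 and H-reflex measures at t3. At t44 and t45 the instruction is: "Perform clinical evaluation tests and electrophysiological recordings as described in Baseline visits". During treatment the only repeat measurements are these: "Reassess transspinal stimulation threshold and locomotor EMG activity at study Intervention visits" t15 and t30. Plans for assessment and collection of outcomes {18a} confirms two assessment times for biomarkers and clinical outcomes, and no visit after t45 is listed.

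Methods for additional analyses {20b} says: "There will be no additional analyses".

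**The concern.** A predictor has to be known before the outcome it predicts. A pre-to-post biomarker change is not known until treatment has ended and the final recordings have been made, and by then the recovery has been measured too. A correlation between the two changes fits several explanations: the biomarker change drove the functional change, the functional change drove the biomarker change, or both followed from a common cause such as treatment arm or training response. It does not tell a clinician which patients will benefit.

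The risk is in reporting. Objective 4 invites any clear correlation from this analysis to be presented as a predictive biomarker. The article specifies the biomarker term as change, so this is a stated analysis that does not answer its stated objective, rather than a detail left open.

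**Working it through.** The article gives no figure for this analysis, so there is none to reproduce. The check is a comparison of the passages, followed by two calculations for scale.

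**1. When each quantity is known**

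| Quantity | Source in the article | Known from |
|---|---|---|
| Baseline biomarker | {13}, t2 and t3 | before treatment |
| Baseline clinical score | {13}, t1 | before treatment |
| Threshold and locomotor EMG | {13}, t15 and t30 | mid-course |
| Biomarker change (post minus pre) | {13}, t2/t3 and t44/t45 | t44/t45 |
| Post-treatment clinical score | {13}, t44/t45 | t44/t45 |

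The analysis named in {20a} uses the fourth row. Its start point is the baseline recording, but the difference is complete only at the visits that also supply the fifth row. The first row comes before recovery and enters no named model.

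**2. A clear change-on-change correlation need not imply a predictor**

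Assumptions (not from the article): biomarker change and clinical change each load 0.7 on a shared factor, all variables have unit variance, and the baseline biomarker is unrelated to either.

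- Expected correlation between the changes: 0.7 × 0.7 = 0.49.
- Expected correlation between baseline biomarker and clinical change: 0.
- Simulation, 4,000 runs each at n = 45 and n = 36: mean change-on-change correlation 0.48 at both sizes; mean baseline-to-change correlation between −0.01 and 0.00.

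Under these assumptions the named analysis shows a solid correlation while the pre-treatment biomarker predicts nothing. The values are illustrative and do not estimate what this trial will find.

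**3. What a baseline-biomarker analysis could detect**

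Inputs: 45 participants and a projected 20% dropout (Sample size {14}), so 45 × 0.8 = 36. Two-sided 5%, 80% power, Fisher z:

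r = tanh[(1.960 + 0.842) / √(n − 3)]

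- n = 45: 2.802 / √42 = 0.432, so r = 0.41 (about 17% of variance).
- n = 36: 2.802 / √33 = 0.488, so r = 0.45 (about 20% of variance).

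These are for one unadjusted test. As an example of multiplicity, take three biomarkers by four walking and balance tests, 12 in all, with Bonferroni: 0.05 / 12 = 0.0042, critical value 2.865, sum 2.865 + 0.842 = 3.707.

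- n = 45: 3.707 / √42 = 0.572, so r = 0.52.
- n = 36: 3.707 / √33 = 0.645, so r = 0.57.

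For MEPmax, Outcomes {12} restricts the analysis to participants with obtainable soleus MEPs at baseline. The article does not say how many that will be, so the detectable correlation is larger than these by an unknown amount.

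**4. Quality of life**

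The term stands in the {20a} regression, and the Discussion lists it among what is measured. The primary, secondary and other outcomes in {12} contain no quality-of-life measure; the questionnaires listed there cover bladder, bowel and sexual function.

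**The case against.** **Prediction is partly covered.** A reader might infer that nothing in the plan addresses prediction. That is not so. The ANCOVA in {20a} carries age, gender, level of injury and baseline walking function, all known before treatment, and objective 4 allows clinical as well as electrophysiological predictors. This stands, and it limits the point to biomarkers.

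**The design provides time order.** A reader might also infer that the design itself rules out a predictor analysis. It does not: baseline biomarkers at t2 and t3 precede the final clinical tests by 40 sessions. Locomotor EMG at t15 and t30 also comes earlier, although it belongs to the other outcomes and not to the primary outcomes that the regression names. The fault is in the choice of analysis variable, not in the data.

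**Condensed text.** Objective 4 does not itself say change, the sentence in {20a} speaks of establishing a relationship, and it does not fix when standing and walking ability is measured. An analysis plan that is not shown might specify baseline predictors. This has some force, but the article does fix the biomarker term as change. No timing of the clinical measure rescues it: with baseline ability in the model, the clinical score would come before the biomarker change, which is not prediction of recovery by a biomarker.

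**The sentence in {20b}.** It is tempting to read it as forbidding a baseline version. It stands under the item on additional analyses, with subgroups as the example, and the correlation is already planned in objective 4. It does not clearly bar the remedy, and the point does not rest on it.

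**Importance.** No primary outcome, randomised comparison, sample size or safety matter depends on this, and predictor is often used loosely for correlate. That is fair, and it is why the remedy is modest.

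**Conclusion.** The point holds for biomarkers. The one biomarker-clinical analysis named would deliver concurrent association, while objective 4 asks for electrophysiological predictors of recovery. This rests on reading the change in {20a} as pre-to-post change, which the two assessment times support, and on there being no follow-up after t45. It does not extend to clinical or demographic predictors, nor does it show that the trial's data are inadequate.

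The consequence is a possible false claim of predictive biomarkers under a secondary objective; the randomised comparisons are untouched. A proper predictor analysis is feasible but modest: it would reliably find only strong predictors, with correlations of about 0.41 to 0.45 for a single unadjusted test and about 0.52 to 0.57 in the 12-test example. The unmatched quality-of-life term is a minor wording matter with no bearing on prediction.

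**What to change.** In {20a}, add for the predictor part of objective 4 a regression of each post-treatment walking or balance score on the baseline biomarker (MEPmax where obtainable, the 1.0/0.1 Hz H-reflex ratio, the conditioned H-reflex), adjusted for the baseline value of that score and for arm. Report it as exploratory, state the number of tests, and give estimates with confidence intervals.

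Keep the change-on-change analysis, adjust it for arm so that a treatment effect on both measures does not by itself create a correlation, and label it concurrent association. If the investigators do not want the baseline analysis, the alternative is to reword objective 4 as association.

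Tie quality of life to a questionnaire that is actually collected, or remove it from the regression.

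The cost is wording and a little analysis. No visit, measurement or participant is added. The downside is a set of exploratory tests at modest n, further reduced for MEPmax, so a null result would not rule out a weaker predictor.
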